**Fig. 1 Fig1:**
[figure not shown]
Description of one cycle involving a PWD and their (in)formal carer

The groups will be stratified on severity of dementia, based on a Global Deterioration Scale (GDS) [54] score of 4 to 6, the person doing the intervention (informal carer who can be a family member or relative; or a formal carer), and nursing home. Residents will be randomized after stratification. Allocation of residents with dementia and (in)formal carers to the experimental or control group will be done via manual drawing of lots by the researchers, and (in)formal carers are informed of the assignments afterwards.

In addition, effects of the experimental intervention versus the control intervention in informal carers will be investigated regarding their feelings of competence. Effects on the (in)formal carers who provide the Photo-Activity intervention (experimental group) or the general conversation sessions (control group) with the residents, are compared regarding attitude and empathy in both groups.

During the trial period, a process evaluation will also be conducted where residents and their (in)formal carers at the end of the 4-week intervention will be asked about their experiences with the implementation of the Photo-Activity intervention, in order to gain insight into factors that may have influenced the study outcomes, such as the user-friendliness and usability of the Photo-Activity app, the frequency of use, and facilitating and impeding factors towards successfully implementing the Photo-Activity intervention. Residents who participated in the general conversation activity and the (in)formal carers who delivered this activity will also be asked about their experiences.

In Phase III, based on the results of the process evaluation, an implementation toolkit will be developed as described in the Objectives.

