### Study setting and participants

The study will be conducted in 14 nursing home wards that are part of 2 large care organizations in the Netherlands (in the Amsterdam and Haarlem region). PWD in these participating nursing home wards who meet the inclusion and exclusion criteria (regardless of gender, age, socioeconomic status, and ethnicity), along with their legal guardians, will receive a written invitation from the nursing home with a consent form for participation and information about the study.

Based on the pilot study with the Photo-Activity, in which large positive effect sizes were found for social interaction (d= 0.86) and reduced negative behaviour (*d*=0.85) using the INTERACT scale [55] during the intervention [35], a power-analysis (power 0.80, α=0.05, *d*=0.8) and expected 10% dropout in 6 weeks, for this explorative study 45 people with dementia are needed per group (total of 90) to find statistically significant large effects. The researchers will promote the project in the care organizations and work with the research coordinators, ward managers and team leaders in order to meet the required recruitment target.

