### Eligibility criteria

#### Inclusion criteria

Residents with dementia (Alzheimer’s disease, vascular dementia, Mixed Alzheimer’s-vascular dementia, front-temporal dementia, Lewy Body disease, or others) whose score range from 4-6 (moderate to severe dementia) on the GDS [54], and have been admitted to the nursing home for at least 1 month are eligible for the study. Those who give their consent and who agree to participate will be included, and after stratification (severity of dementia; intervention provider; and nursing home), will be randomly assigned to an experimental or control group. Formal carers will also be randomly assigned to deliver the experimental or control activity.

For the informal carers, they will be assigned to the same activity where their loved one is randomly assigned to, and there are no specific inclusion criteria, except that they are willing to participate in the study themselves as well as to provide information on the interests of their loved one. If they would like to be involved in carrying out the Photo-Activity or control intervention for their loved one, they additionally must be willing to participate in a short training to deliver the intervention and be able to commit to providing the intervention for 2 half hour sessions a week, for a period of 1 month.

The formal carers of the included PWD’s are invited and trained to deliver the experimental/control intervention and to be a part of the study after providing informed consent. The recruitment of formal carers will focus on those who work enough hours to fulfill the criteria of delivering the experimental or control activity twice a week for 4 weeks. Information about characteristics of the formal carers delivering the intervention (work function, training level, experience, working hours, etc.) will be collected.

For formal carers assigned to be Independent Assessors, i.e. not involved in the interventions, recruitment criteria are that they are present in the ward for more than 2 days a week, and have regular contact with the residents. The Independent Assessors are asked to complete outcome measures about the residents. Because no information is collected on the Independent Assessors themselves, they are not asked to fill out the consent forms.

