## Interventions and procedures

### Photo-activity intervention (experimental group)

#### Training

The (in)formal carers assigned to the experimental group, will be informed about the background, method, and application of the Photo-Activity intervention app, by a member of the research team. A short video from the artist [name], who originally developed the intervention, will also be shown.

A 75-minute training session on how to hold conversations around the artistic photographs with the residents will be given by a senior member of the research team. The training will include basic interview techniques that foster rapport, like asking open questions instead of closed ones, reflective listening and summarizing. The (in)formal carers in the experimental group will also be trained to use ‘person-enhancing communication strategies’ such as offering comfort (in the form of warmth, security, and conversing in a relaxed pace), supporting identity (through respect and acceptance), and offering opportunities for attachment (recognition, affirmation, sincerity) as opposed to ‘predatory communication strategies’ such as withholding comfort (being intimidating, abstaining, speeding up the conversation), not supporting identity (childish, labelling, belittling), and not allowing oneself to be attached (accusing, deceiving, not acknowledging) [4]. Finally, they will also be instructed to avoid questions that would seem to ‘test’ the residents about their interests or to recognize certain photos; rather any response from the residents is acceptable i.e. there is no right or wrong. The (in)formal carers are informed that all the information on ‘person enhancing communication strategies’ can also be found in the Photo-Activity app.

(In)formal carers participating in the training will be given their own unique code to access the app, besides a unique code they receive for each resident to which they provide the Photo-Activity. They will be invited to spend time on the app in order to familiarize themselves with the functions, i.e.: selecting a series of photos based on the interests profile of the resident with dementia, saving photos in the ‘conversation basket’, showing the photo series in full screen presentation mode, selecting favorite photos, or taking notes about photos that elicited the most/least reactions, or were more/less appreciated by the resident.

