## Analysis

### Quantitative data

Analysis for quantitative data will be done using SPSS for Windows. Participant characteristics are analyzed with descriptive statistics and differences are tested with parametric or non-parametric tests dependent on type of data. Multilevel analysis (MLA) is performed to investigate whether the averages on continuous outcome measures at T1 and T2 differ between experimental and control groups. Baseline measurements (T0), severity of dementia and potential confounders are included in the analyses as covariates. The MLA takes into account the clustering of people with dementia and caregivers within nursing wards. The same procedure is used for dichotomous data, but the analyses are then performed with General Estimations Equations. Both intention-to-treat and ‘per protocol’ analyses will be done.

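### The multilevel model names only the ward as a clustering unit; where a formal carer serves several residents in one arm, standard errors will be too small, chiefly for INTERACT

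*Protocol article*

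**What the plan says.** In the protocol article, Analysis (Quantitative data), the clustering statement is: "The MLA takes into account the clustering of people with dementia and caregivers within nursing wards". Residents and caregivers stand side by side as units inside wards; no level places residents within the carer who treats them. Binary outcomes follow suit: "The same procedure is used for dichotomous data, but the analyses are then performed with General Estimations Equations".

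Three other places describe how delivery is organised:

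- Inclusion criteria, on formal carers: "Formal carers will also be randomly assigned to deliver the experimental or control activity". Each formal carer therefore belongs to one arm.
- Photo-Activity Training, on app access: each carer gets a personal code, "besides a unique code they receive for each resident to which they provide the Photo-Activity". The arrangement allows for more than one resident per carer, and no section caps the number at one.
- Inclusion criteria, on informal carers: "they will be assigned to the same activity where their loved one is randomly assigned to". An informal carer is tied to one resident.

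Provider type and nursing home are stratification factors (Methods/Design): "the person doing the intervention (informal carer who can be a family member or relative; or a formal carer), and nursing home". On setting, Study setting and participants says: "The study will be conducted in 14 nursing home wards", with 90 residents in total.

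**The concern.** This is the usual provider-clustering problem in a trial of an activity delivered by people. Some carers draw residents out better than others. If one carer treats several residents, their outcomes share that carer's skill and rapport and are positively correlated. Because the carer works in one arm only, the shared component does not cancel between arms; it adds to the variance of the treatment contrast.

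A ward intercept does not solve this. Where a ward holds residents of both arms, the ward effect largely drops out of the comparison, while the carer effect stays in. A model with ward as its only random effect then treats residents of the same carer as independent given ward. Its confidence intervals are too narrow, and an unusually good carer in one arm can pass for an effect of the activity.

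INTERACT is the most exposed outcome. It is primary, and it scores the resident's mood and social interaction with the delivering carer during the session. SFAS is self-reported by the resident but is collected by the delivering carer around the session, so it may be affected too. QUALIDEM and NPI-Q are rated by Independent Assessors who neither deliver nor attend the sessions, so delivering-carer correlation is probably weaker there.

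**Working it through.** **The plan's own figures.** The protocol gives no ICC, caseload or design effect, so there is no clustering figure to reproduce. Its sample size enters only the power check in step 5.

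**Inputs from the protocol.** 90 residents, two arms of 45, 14 wards, 10% dropout, d = 0.8, α = 0.05 (taken as two-sided). 90/14 = 6.4 residents per ward, or about 3 per arm per ward.

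**Assumptions, because the protocol is silent.** Residents per formal carer, m = 1 to 4; carer ICC 0.01 to 0.3; share of residents treated by formal carers, all or half; both arms present in each ward.

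**Step 1: simple design effect.** DEFF = 1 + (m − 1) × ICC, and true α = 2 × [1 − Φ(1.96/√DEFF)].

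| m | ICC | DEFF | SE ratio | true α |
|---|---|---|---|---|
| 1 | any | 1.00 | 1.00 | 5.0% |
| 2 | 0.10 | 1.10 | 1.05 | 6.2% |
| 2 | 0.30 | 1.30 | 1.14 | 8.6% |
| 3 | 0.01 | 1.02 | 1.01 | 5.2% |
| 3 | 0.05 | 1.10 | 1.05 | 6.2% |
| 3 | 0.10 | 1.20 | 1.10 | 7.4% |
| 3 | 0.20 | 1.40 | 1.18 | 9.8% |
| 3 | 0.30 | 1.60 | 1.26 | 12.1% |

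**Step 2: the ward-adjusted comparison itself.** Take 14 wards, one formal carer per arm per ward and 3 residents each (84 residents), with total variance 1 apart from ward. Write r for the carer ICC.

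- True SE = √[2 × (r + (1 − r)/3)/14].
- Removing ward leaves 84 − 14 − 1 = 69 degrees of freedom. The expected residual variance is [56 × (1 − r) + 13 × (1 − r + 3r)]/69.
- SE reported by the ward-only analysis = √(residual variance × 2/42).

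For r = 0.2, true SE = √[2 × (0.2 + 0.2667)/14] = 0.258. Residual variance = (44.8 + 18.2)/69 = 0.913, so reported SE = √(0.913 × 2/42) = 0.209. The ratio is 1.24 and the true α 11.2%. The same steps give 6.4% at r = 0.05, 7.9% at 0.1 and 14.6% at 0.3. These exceed step 1 because the ward term takes up part of the carer variance, which lowers the reported SE further.

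**Step 3: simulation under no effect.** The step 2 design with ward removed rejects 6.5%, 8.0%, 11.3% and 14.6% at ICC 0.05, 0.1, 0.2 and 0.3. A separate REML simulation with a ward random intercept only (ward ICC 0.05) rejects 5.1% at carer ICC 0, then 6.9%, 7.7% and 12.3% at 0.05, 0.10 and 0.20. True SE over model SE is 1.01, 1.06, 1.11 and 1.27. The error rate is nominal without a carer effect and rises with it, so carer clustering is the cause.

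**Step 4: dilution by informal carers.** With half the residents treated by informal carers and up to 3 residents per formal carer, the same design rejects 5.2%, 5.7%, 6.9% and 6.9% at ICC 0.05, 0.1, 0.2 and 0.3. With at most 2 per formal carer it rejects 5.1-6.2%.

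**Step 5: power if carers are modelled.** Completers per arm: 45 × 0.9 = 40.5. Power at d = 0.8 is 0.95 with DEFF 1. At DEFF 1.6 (m = 4, ICC 0.20) the effective number is 40.5/1.6 = 25.3 per arm and power is 0.81. N = 90 therefore still carries the target effect over m = 2-4 and ICC 0.01-0.20. The stated inputs give only 25 per arm, or 28 after dropout, so 45 is not reproduced. That is a separate matter, and the protocol does not describe the surplus as an allowance for clustering.

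**The case against.** The strongest reply is that the Analysis sentence lists no random effects and does mention caregivers, so it might be meant to include a carer level. That reading is possible but not the natural one. The sentence puts caregivers next to residents as units within wards, which fits carers being analysed in their own right on ADQ, IRI and SSCQ. A ward-only model would comply with the text. If a carer level is intended, one sentence settles it.

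The second reply is that shared carers are permitted rather than described. The only support is the app-code wording. Elsewhere a session is described as a resident and their carer, and formal carers are recruited to deliver twice a week, which is one resident's schedule. This stands, and it makes the finding conditional.

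The third is that informal carers contribute no shared-carer clustering. This also stands, and step 4 shows how much it matters.

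Several stronger readings are tempting but go beyond the document:

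- A reader might infer that standard errors are certainly too small, or that false-positive rates are 8-15%. Without a caseload, an ICC or a formal-carer share, those figures are the upper end of an assumed range.
- A reader might infer equal damage to INTERACT, QUALIDEM, SFAS and NPI-Q. Who rates each outcome argues against that.
- A reader might take both arms to be present in every ward. The protocol stratifies by nursing home and speaks of residents of both groups in a ward, so mixing is likely, but it is not guaranteed ward by ward.
- A reader might fault the silence on degrees of freedom, on a resident-level effect across T1 and T2, or on one ADQ and IRI record per carer. Such detail is commonly left to an SAP, and nothing says that ADQ or IRI will be analysed per resident.

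**Conclusion.** The point holds conditionally. The stated clustering unit is the ward, formal carers are allocated to one arm, and the design allows a carer to serve several residents. If formal carers do share residents and carers differ in their effect, the ward-only multilevel model understates the standard error, above all for INTERACT.

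The size depends on three quantities that the protocol does not give. True type I error is about 5% with one resident per carer, a low ICC or many informal carers. It is about 6-8% with three residents per carer and ICC 0.05-0.10, and about 11-15% if all residents have formal carers with three residents each and ICC 0.2-0.3. The last range is a worst case, not an estimate for this trial. The change is worth making because it is cheap and does no harm if the carer variance proves to be zero.

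**What to change.** State in the Analysis section that the multilevel model for resident outcomes includes a random intercept for the delivering carer within ward, with each informal carer entered as a cluster of one. State that the GEE for binary outcomes accounts for the same clustering. A robust variance with ward as the cluster would in principle already cover residents who share a carer inside a ward, although it would rest on only 14 clusters; a model-based variance would not.

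The cost is one more variance component and somewhat wider confidence intervals. Delivering carers are already study participants and keep session records, so the link from resident to carer should be available without new data collection. By step 5, power at d = 0.8 stays at 0.81 or above over m = 2-4 and ICC 0.01-0.20.

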### Qualitative data

Descriptive statistics via SPSS for Windows will be used to analyze the characteristics of the interviewees, care providers and other stakeholders. Audio recordings from focus groups will be transcribed. The transcriptions and meeting notes of the focus groups and interviews with (in)formal carers, and stakeholders will be analyzed thematically using deductive and inductive methods [84]. The software Atlas.ti will be used.

### Ancillary and post-trial care

If the participating nursing homes view the Photo-Activity intervention as a positive addition to their services, then the (in)formal carers will be given free access to the web-app after the study period is completed, to avoid data of active and non-active study participants being collected in Google Analytics. However, for residents in the Photo-Activity, they will still be able to use the web-app after follow-up at T2, because the researchers will have a record of the Photo-Activity session times that they can match to Google Analytics.

Training on the use of the web-app and the Photo-Activity intervention will also be made available to nursing staff of the participating nursing homes who are interested in the Photo-Activity, but provided the control intervention or were not involved in providing the interventions. If the intervention proves to be effective, an implementation toolkit will be developed to promote further implementation in the participating nursing homes, as well as dissemination to other nursing homes across the country.

### Dissemination policy

Results of the current study are expected to be available in Spring 2023. The project is linked to the Marie Curie Innovative Training Network DISTINCT, in which 15 early-stage researchers at 10 universities in 7 countries are researching the use of technology to promote social health in people with dementia and their carers. This has given the project international attention right from the start. Via the DISTINCT website and project partner Alzheimer Europe, results are easily disseminated internationally. Research results will be published in open-access and national/international scientific professional, and public (online) journals for nursing, gerontology, psychiatry and technology. Because the project was classified by the Medical Ethics Review Committee of VUmc as non-medical research, any amendments made to the protocol will be noted and written in the final reporting of the study.

## Discussion

With the accessibility and convenience of tablet-computers, the digital, person-centered Photo-Activity intervention is expected to be a simple and user-friendly activity for formal and informal carers alike to provide to PWD living in nursing homes and other residential care settings. The web app can be accessed via internet browsers on tablets or mobile phones, and thus can be easily used and brought to any space (living rooms or bedrooms) in the nursing home. It is expected that the Photo-Activity intervention will enable the PWD to connect meaningfully with their (in)formal carers through a social activity that acknowledges their personal interests and respects their personhood. At the same time, this activity provides a playful way for (in)formal carers to engage with the residents, as often, they are uncertain about how they can have conversations with residents who are in an advanced stage of dementia.

Ultimately, it is expected that the resident, through feeling seen and acknowledged as a person, will experience improved mood and wellbeing as a result of the digital Photo-Activity intervention. It is expected that their informal carers will be more accepting of the transferring of care responsibilities to the nursing home when experiencing the person-centered care approach and improved relationship with their loved one’s care provider. It is expected that the formal carers will be able to use the digital photo intervention as a tool to help them work in a more person-centered way, and allow them to develop a deeper personal relationship and more empathy for the residents. The implementation toolkit provided by the project will help to implement and scale up the intervention in other care and home situations.

Finally, as an intervention aiming to harness the potential of technology, this study can provide insight into the use of technological devices to support and promote person-centered care for the improvement of the social and mental health of residents with dementia in long term care facilities.

## Data Availability

Not applicable.

## Abbreviations

ADQ: Approaches to Dementia Questionnaire
APH: Amsterdam Public Health research institute
Atlas.ti: Software package for qualitative data analyses and mixed methods research
Castor EDC: Castor Electronic Data Capture platform
DISTINCT: Dementia: Intersectorial Strategy for Training and Innovation Network for Current Technology
Foundation for Support VCVGZ: In Dutch - Stichting tot Steun VCVGZ (Vereniging voor Christelijke Verzorging van Geestes en Zenuwzieken), a charitable foundation
HBO: in Dutch- *Hoger Beroeps Onderwijs;* or University of applied sciences
INTERACT: Behaviour observation scale for social interaction
ITN: Innovative Training Network
GCP: Good Clinical Practice
GDS: Global Deterioration Scale
GGZ inGeest: Regional Dutch mental health service in Amsterdam
MBO: in Dutch- *Middelbaar Beroeps Onderwijs*; secondary vocational education
MRC: Medical Research Council
Non-WMO: The Medical Research Involving Human Subjects Act (WMO) does not apply to the study
NPI-Q: Neuropsychiatric inventory questionnaire
PWD: Persons with dementia
QUALIDEM: Dementia-specific, quality of life instrument
RCOAK: In Dutch- *Roomsch Catholijk Oude Armen Kantoor;* a charitable Catholic Foundation
RCT: Randomized controlled trial
SPSS: Statistical Package for the Social Sciences
SSCQ: Short Sense of Competence Questionnaire
T0: Baseline
T1: Four weeks after the start of the intervention period
T2: Two week follow-up after T1
TOPICS-MDS: The Older Persons and Informal Caregivers Survey Minimum Data Set
V+I+P+S: Valuing people with dementia and those who care for them
VUmc: VU University Medical Centre
